### Randomization

Patients are randomized prior to surgery in the doctor's office by computerized block randomization for either plate fixation or ESIN. The block varies between 2, 4, 6 and 8 patients. In each block the two operative techniques are equally represented. This randomization procedure will be stratified by participating hospital. After randomization, follow-up of patients will take place according to the intention-to-treat principle.

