### Sample Size and Power

The primary outcome measure in this study is the DASH score. Initially, a minimum difference of 10 points in DASH score can be considered as clinically relevant [16]. However the DASH score rates the whole upper extremity and a smaller difference should be considered as clinically relevant when focusing on clavicular function in particular.

Unfortunately, no studies comparing plate fixation and ESIN for dislocated midshaft clavicular fractures with power calculation are available [14]. Therefore we performed a power calculation based on the following rationale. A DASH score of a "normal" upper extremity varies between four and eight [15]. The DASH score of the group of patients who were conservatively treated for DMCF after 24 weeks was 14 [12]. We consider the difference of six points between this latter DASH score and the worst score (eight) within the normal range as the clinically relevant margin. This coincides well with a recently online published protocol for treatment of wrist fractures in which a comparable margin in DASH score for local function (five points) is considered clinically relevant (Design Minimax studie: http://www.cruamc.nl/Minimax). With an expected standard deviation of 11 points in the DASH score, a two sided alpha of 0.05 and a power of 0.80, 53 patients in each group are needed (total 106) to show a difference of at least 6 points in DASH score after 6 months. Considering that an interim analysis is planned (see below), it is assumed that 2 sequential tests are made using the O'Brien-Fleming spending function to determine the test boundaries. Further assuming a 10% loss to follow-up, 120 patients should be included.

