### Statistical Methods

Data will be analyzed according to the intention-to-treat principle. The difference between the operative techniques at the end of the follow-up period in DASH (primary outcome) and Constant scores will be tested for significance using the Student's T-test or the Mann-Whitney U test, depending data distributions. A general linear random effects model will be applied to assess differences during the follow-up period in DASH, Constant, pain, and SF-36 scores to account for repeated measures within patients. The difference in the frequency of complications during follow-up will be assessed with Poisson regression, whereas the Chi-square test or Fisher's exact test will be used to test for differences in proportion of re-operated patients. Differences in cosmetic satisfaction will be tested using the Mann-Whitney U-test. Time to radiological consolidation will be assessed by Kaplan-Meier analysis. A p-value of < 0.05 will be considered statistically significant in all analyses. SPSS software will be used for statistical analysis.

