### Data and safety monitoring board and interim analysis

A data and safety monitoring board (DSMB) is established existing of two surgeons and one methodologist. The DSMB will perform an interim analysis after one year. In the interim analysis discrepancies in a) major complications, b) minor complications and c) DASH scores between both procedures are calculated.

Major complications are defined as intra-operative nerve or vessel damage resulting in prolonged hospital admission, persistent injury or death, and re-operation due to an unsatisfying result. Minor complications are the other complications listed in table 3.

After one year, 72 patients (36 patients in each arm) will be included if inclusion is moving on as expected. The following stop criteria are defined:

* an established difference in patients with major complications of 13.5% (1% in one arm against 14.5% in the other) with a two-sided p-value of 0.1, 80% power, and assuming a negligible mortality rate, or

* an established difference in patients with minor complications of 37.1% (15.5% in one arm against 52.6% in the other arm) with a two-sided p-value of 0.01 and 80% power, or

* an established difference in DASH-score with an effect size of 0.55 with a two-sided p-value of 0.003 and 16.5% power (reflecting the first of the 2 sequential tests for the primary outcome using the O'Brien-Fleming spending function), or

* a potential difference in mortality, at the discretion of the DSMB.

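### The blanket p < 0.05 rule contradicts the two-look O'Brien-Fleming design for the primary DASH test; the excess error is small (about 0.0510 against 0.05)

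*Protocol article*

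**What the plan says.** Three sections of the protocol article bear on the significance level for DASH.

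- **Sample Size and Power** derives the sample size from "a two sided alpha of 0.05 and a power of 0.80, 53 patients in each group are needed (total 106" in all). On the planned interim look it adds that "it is assumed that 2 sequential tests are made using the O'Brien-Fleming spending function to determine the test boundaries".
- **Data and safety monitoring board and interim analysis** lists a DASH difference as one of its stop criteria, with an effect size of 0.55, a two-sided p-value of 0.003 and 16.5% power. It describes this criterion as "reflecting the first of the 2 sequential tests for the primary outcome using the O'Brien-Fleming spending function".
- **Statistical Methods** names DASH as the primary outcome, gives the tests for the primary and secondary outcomes, and ends: "A p-value of < 0.05 will be considered statistically significant in all analyses". It makes no exception for the final DASH test.

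**The concern.** Under a spending function, the levels of the two tests share one total of 0.05. A first test at 0.003 leaves a second level below 0.05. The sentence in Statistical Methods gives the final DASH test the full 0.05 as well, so the two rules cannot both hold. A final p-value of 0.0495, for example, would be significant under the blanket rule but not under the sequential design at half information.

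The test affected is the one confirmatory test of the trial, and the error always runs in the anti-conservative direction. An analyst would normally take the significance level from Statistical Methods, where the unqualified rule stands.

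**Working it through.** **Inputs from the protocol article**
- Two-sided alpha 0.05, power 0.80, SD 11, difference 6 points, two tests with O'Brien-Fleming spending, 10% loss, 120 patients (Sample Size and Power).
- Equal allocation (Randomization).
- Interim DASH level 0.003 with 16.5% power at effect size 0.55; 72 patients included after one year (interim analysis section).
- Final level 0.05 (Statistical Methods).
- The information fraction t at the interim is not stated. It is inferred in step 2 and varied in step 4.

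**1. The stated sample size.** n per group = 2 × (z₀.₉₇₅ + z₀.₈₀)² × (SD/difference)² = 2 × (1.960 + 0.842)² × (11/6)² = 52.8, so 53 per group and 106 in total. The plan's figure is reproduced.

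**2. The stated interim level and its information fraction.** The O'Brien-Fleming-type spending function for two-sided alpha (twice a one-sided 0.025) is α(t) = 4 × [1 − Φ(z₀.₉₈₇₅/√t)]. At t = 0.5 it gives 4 × [1 − Φ(2.241/0.707)] = 0.00305, which matches 0.003. Half of 53 is 26.5 per arm. Power there at two-sided 0.003 (critical value 2.968) is Φ(d × √(26.5/2) − 2.968), which is 16.3% for d = 6/11 and 16.7% for d = 0.55. The plan states 16.5%. Both interim figures therefore point to t = 0.5. With 36 per arm the same formula gives about 26%, so the stated power does not describe 72 patients with DASH data.

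**3. Overall error at t = 0.5.** Under the null hypothesis the two test statistics are approximately bivariate normal with correlation √t. The overall error is 1 − P(|Z₁| < c₁ and |Z₂| < c₂).
- With c₁ = 2.968 (p = 0.003) and c₂ = 1.960 (p = 0.05), it is 0.0510.
- Solving for the final level that makes it exactly 0.05 gives 0.0490.

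**4. Range over the unstated information fraction, interim level held at 0.003**

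| t (assumed) | Overall error with final 0.05 | Final level needed for overall 0.05 |
|---|---|---|
| 0.30 | 0.0518 | 0.0482 |
| 0.40 | 0.0514 | 0.0486 |
| 0.50 | 0.0510 | 0.0490 |
| 0.60 | 0.0506 | 0.0494 |
| 0.68 (36/53) | 0.0503 | 0.0496 |

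The overall error exceeds 0.05 in every row, by 0.03 to 0.18 percentage points.

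**5. Power.** With 53 per arm, t = 0.5 and the interim look at 0.00305, overall power is 0.8027 with a final level of 0.05 and 0.8003 with 0.049. The difference is 0.24 percentage points, and power stays at 80%.

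**The case against.** **The intent is already clear.** The sample size section says that the spending function sets the boundaries, in the plural, and a specific rule would normally override a general closing sentence. The blanket rule cannot be meant for every DASH test, because the interim one has its own 0.003. The total of 120 also fits a corrected final level: at 0.049 the formula gives 53.09, so 54 per arm, and 108/0.9 = 120, whereas 106/0.9 = 117.8, or 118. This is suggestive and not proof. It supports reading the sentence as loose wording, but the sentence remains unqualified and conflicts with the design.

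**The second boundary belongs in the analysis plan.** This stands. The final critical value depends on the information observed at the interim, and a condensed article may leave it out. The point is therefore not that a boundary is missing. It is that an explicit level is stated and is wrong for the primary test.

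**The effect is very small.** This also stands. The choice between a t-test and a Mann-Whitney test, which the plan leaves to the data distribution, could move a borderline p-value by more than 0.001.

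**A larger effect might be inferred.** From the 72 patients, a reader might take t = 0.60 (72/120) to 0.68 (36/53), recompute the interim level from the spending function (0.0076 to 0.0131), and arrive at an overall error of 0.0523 to 0.0537 with a required final level of 0.0476 to 0.0460. The documents do not support this. They fix the interim level at 0.003, and they say that 72 patients will have been included, not that 72 will have a six-month DASH score. Patients included in the preceding six months cannot have one. Recomputing at smaller fractions shrinks the problem: at t = 0.40 the interim level would be 0.0008 and the overall error 0.0503, and at t = 0.30 the error would be 0.0500.

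**Conclusion.** The inconsistency is real and minor. Taken as written, the rule in Statistical Methods gives an overall two-sided error of about 0.0510 at the design fraction of one half, where a final level of 0.0490 is needed. No stated figure is miscalculated: the 53 per group, the 0.003 and the 16.5% all reproduce. Nor do the documents support a claim that the sample size is inadequate or that the error rate is materially inflated.

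The result rests on three assumptions: the interim DASH test is run at the stated 0.003; crossing that level can stop the trial and counts as a claim of a difference, as its place among the stop criteria indicates; and the normal approximation holds for the two test statistics.

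**What to change.** Replace the last rule on significance in Statistical Methods with wording such as: *The final test of the primary DASH outcome uses the second sequential boundary, computed from the interim boundary actually applied and the information fraction actually observed, so that the overall two-sided alpha is 0.05 (p < 0.049 if half of the information was available and the interim level was 0.003). For all other analyses, p < 0.05 is considered statistically significant.*

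The change should be made before the final data are seen. It needs one sentence of amendment, and the sample size of 120 stays as it is.

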### Data and safety monitoring board and interim analysis

A data and safety monitoring board (DSMB) is established existing of two surgeons and one methodologist. The DSMB will perform an interim analysis after one year. In the interim analysis discrepancies in a) major complications, b) minor complications and c) DASH scores between both procedures are calculated.

Major complications are defined as intra-operative nerve or vessel damage resulting in prolonged hospital admission, persistent injury or death, and re-operation due to an unsatisfying result. Minor complications are the other complications listed in table 3.

After one year, 72 patients (36 patients in each arm) will be included if inclusion is moving on as expected. The following stop criteria are defined:

* an established difference in patients with major complications of 13.5% (1% in one arm against 14.5% in the other) with a two-sided p-value of 0.1, 80% power, and assuming a negligible mortality rate, or

* an established difference in patients with minor complications of 37.1% (15.5% in one arm against 52.6% in the other arm) with a two-sided p-value of 0.01 and 80% power, or

* an established difference in DASH-score with an effect size of 0.55 with a two-sided p-value of 0.003 and 16.5% power (reflecting the first of the 2 sequential tests for the primary outcome using the O'Brien-Fleming spending function), or

* a potential difference in mortality, at the discretion of the DSMB.

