#### Operative procedure ESIN using a TEN

Patients are administered prophylactic antibiotics. With a general anesthetic, the patient is placed in supine position. A small skin incision is made approximately 1 centimeter lateral to the sternoclavicular joint. The anterior cortex is opened with a sharp pointed reamer while care is being taken to not accidentally perforate the thorax. A TEN is inserted (the diameter varies from 2 to 3,5 mm, dependent on the width of the bone). Closed reduction, eventually supplemented with two percutaneously introduced pointed reduction clamps, is performed under fluoroscopic control. If closed reduction fails, an additional incision will be made above the fracture site for direct manipulation of the main fragments. After complete introduction of the TEN in the lateral fragment, the fracture is compressed and the TEN will be cut as short as possible at the medial end. The fascia and the skin are closed in layers.

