### Follow-up

The patient is requested to record - on a daily basis during the fortnight immediately following surgery - the pain experienced as well as the type and amount of analgesics used. Experienced pain is assessed with a 10-point Likert scale (0 = no pain and 10 = extremely painful).

All patients are reviewed in the outpatient department by the treating surgeon and investigator at 2 and 6 weeks, 3 and 6 months and 1 year after surgery. All visits include standardized clinical evaluation and registration of possible complications by the treating surgeon and the investigator (table 3).

**Table 3 T3:** Complications

Intra-operative complications	Post-operative complications
- Nerve/vessel damage	- Wound healing disorders (infection, hypertrophic scar, dehiscence)
- Other operative complications	- Transient brachial plexus laesion (defined as paresthesia of the arm, and weakness of the pink and index finger)
	- Irritation of the implant (post-operative pain/itch/redness/irritation)
	- Migration of the implant
	- Breakage of the implant
	- Non-union (defined as lack of radiographic healing with clinical evidence of pain and motion at the fracture site after 6 months)
	- Mal-union (defined as union of the fracture in a shortened, angulated, or displaced position with weakness, easy fatigability, pain with overhead activity, neurologic symptoms, and shoulder asymmetry)
	- Other complications

At the 2 weeks outpatient visit the pain diary is discussed by the researcher with the patient. Radiographs will be taken in order to check implant position and, at subsequent follow-up visits until radiographic union. Radiographic union is defined as complete cortical bridging between proximal and distal fragments on both radiographs as determined by the treating surgeon.

The Disabilities of the Arm, Shoulder and Hand (DASH) and Constant scores will be gathered at the 6 weeks, 3 and 6 months and 1 year postoperative visits by the investigator [15-17].

The DASH questionnaire is a self administered region-specific outcome instrument developed as a measure of self-rated upper extremity disability and symptoms. The DASH questionnaire consists mainly of a 30-item disability/symptom scale, scored 0 (no disability) to 100 (= completely disabled upper extremity) [15,16]. To prevent bias, the DASH questionnaires will be completed in absence of the operating surgeon, before the clinical assessment.

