## Discussion

No comparative prospective or randomized study has been published comparing outcome of plate fixation with ESIN with a TEN of DMCF. The study aim is to provide and compare results of plate fixation and ESIN with a TEN.

Traditionally DMCF were treated conservatively. This policy was based on good results from large cohort series from the sixties: non union rates were < 1% [3,4].

These series, however, were all very mixed with regard to age, clavicular fracture site, displacement and fracture classification. Children, who have better bone healing and remodelling mechanisms, were also included. Malunion was not yet accepted as a clinical entity. Outcome was surgeon based contrary to present-day patient based outcome tools like DASH and Constant scores.

Surgical treatment however, has its own drawbacks. Wound healing disorders, infections, loss of fixation and nonunions do also occur as listed in table 3[12,13,19-22]. In addition, a second surgical procedure might be required to remove the implant. Nevertheless, recently published studies reporting lower nonunion rates, improved functional outcome, faster mobilization and (perhaps therefore) increased patient satisfaction initiated a tendency towards surgical treatment of DMCF [8,12,13,22].

Theoretically, both plate fixation and ESIN have their own advantages. A biomechanical study shows that plate fixation provides a more rigid stabilization compared to ESIN. Therefore plate fixation may provide a stronger construct for early rehabilitation protocols [23]. Plate fixation is technically easy to perform which provides another advantage.

On the other hand, ESIN is less invasive, results in lesser implant prominence and implant removal can be done with minimal dissection [22]. If closed reduction is possible, this technique has the advantage of an intact fracture hematoma, which could speed up the healing process. However, minimally invasive techniques exert certain specific risks that can lead to complications (e.g. for the clavicle iatrogenic brachial plexus injury have been described [20]). The primary endpoint of this study is the DASH score 6 months after surgery. After 6 months the nonunion rates can be calculated and therefore 6 months is the first possible endpoint to determine the success rate of the surgery. Patients will be followed for a 1 year period, mainly to asses the follow-up of nonunions or other implant-related complications.

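### The DSMB's major-complication class is a closed list that omits serious intra-operative events other than nerve or vessel damage, such as the thoracic perforation named as an ESIN hazard, so these count as minor at the interim look

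*Protocol article*

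**What the plan says.** The section on the data and safety monitoring board and interim analysis divides complications into two classes. For the first: "Major complications are defined as intra-operative nerve or vessel damage resulting in prolonged hospital admission, persistent injury or death, and re-operation due to an unsatisfying" […]. For the second: "Minor complications are the other complications listed in table 3". Each class has its own stop criterion:

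- Major: a 13.5-point difference (1% against 14.5%) at a two-sided p of 0.1.
- Minor: a 37.1-point difference (15.5% against 52.6%) at a two-sided p of 0.01.

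DSMB discretion is written in for mortality only. On the size of the interim look: "After one year, 72 patients (36 patients in each arm) will be included if inclusion is moving on as expected".

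Table 3 (Follow-up) has two intra-operative items, "Nerve/vessel damage" and "Other operative complications". Its only post-operative plexus item is "Transient brachial plexus laesion (defined as paresthesia of the arm, and weakness of the pink and index finger". The rest of the post-operative column covers wound, implant and union problems and a catch-all.

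Two other places name hazards of the nailing technique. The ESIN procedure asks that "care is being taken to not accidentally perforate the thorax". The Discussion, on risks of minimally invasive techniques, says that "for the clavicle iatrogenic brachial plexus injury have been described".

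**The concern.** The severity test (longer admission, lasting injury or death) is attached to one kind of damage in one time window. Anything outside that window is minor by default, however serious, unless it is re-operated or fatal.

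Thoracic perforation is the clearest case. The protocol warns of it in the ESIN procedure and not in the plate procedure, and its only place in Table 3 is the intra-operative catch-all. A perforation that keeps a patient in hospital is then pooled with hypertrophic scars and implant irritation and judged at p 0.01, with a 37-point difference in view.

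A second, narrower gap concerns the plexus. A lesion first noted after surgery that then persists does not fit the transient item, so it goes to the post-operative catch-all and is also minor.

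At stake is whether the criterion meant for serious harm can respond to a harm the protocol itself anticipates in one arm.

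**Working it through.** **Inputs from the protocol.** n = 36 per arm; major 1% v 14.5% at two-sided 0.1; minor 15.5% v 52.6% at two-sided 0.01; stated power 80% for each.

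**Step 1: reproduce the stated power.** Let A ~ Bin(36, p1) and B ~ Bin(36, p2). Power = Σ P(A=a)·P(B=b) over all (a, b) for which the uncorrected Pearson chi-square gives p below the threshold.

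- Major: 0.801.
- Minor: 0.801.

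Both match the stated 80%, so the uncorrected chi-square is used below. Fisher's exact test gives 0.500 and 0.726 and is shown as a sensitivity check.

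**Step 2: classify the events under the written definition.**

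| Event | Table 3 item | Class as written |
|---|---|---|
| Intra-operative plexus damage that persists or prolongs admission | Nerve/vessel damage | Major |
| Thoracic perforation with prolonged admission, no re-operation | Intra-operative catch-all | Minor |
| Plexus lesion first recorded after surgery, persistent | Post-operative catch-all | Minor |
| Any event leading to re-operation for an unsatisfying result | – | Major |
| Any death | – | Mortality criterion, DSMB discretion |

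**Step 3: how the class changes the chance of reaching the p-threshold.** Assumptions: the serious event occurs only in the ESIN arm, at rate x, independently of the background; the background in both arms is the protocol's lower rate (15.5% minor, 1% major). The ESIN rate is then b + x − b·x.

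- x = 5%: minor 0.155 + 0.05 − 0.00775 = 0.197; major 0.01 + 0.05 − 0.0005 = 0.0595.
- x = 10%: minor 0.155 + 0.10 − 0.0155 = 0.2395; major 0.01 + 0.10 − 0.001 = 0.109.

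Putting these rates into the Step 1 sum (Fisher in brackets):

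| Excess x | Classed minor, p < 0.01 | Classed major, p < 0.1 |
|---|---|---|
| 0 | 0.8% (0.3%) | 0.8% (0.0%) |
| 2% | 0.9% (0.4%) | 6.7% (0.3%) |
| 5% | 1.6% (0.8%) | 26.9% (4.3%) |
| 10% | 4.3% (2.4%) | 62.9% (27.2%) |

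**Step 4: smallest imbalance that reaches each p-value.** χ² = N(ad − bc)² / (product of the four margins), with N = 72.

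- Major, 0 v 3: 72 × 108² / (36 × 36 × 3 × 69) = 3.13, p = 0.077. The difference is 3/36 = 8.3 points, below the stated 13.5. Fisher needs 0 v 5.
- Minor, 6 v 17 (6/36 being close to 15.5%): 72 × 396² / (36 × 36 × 23 × 49) = 7.73, p = 0.005. The difference is 11/36 = 30.6 points, below the stated 37.1. Fisher needs 6 v 18.

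These counts meet the p-values only. If the stated differences must be observed as well, both criteria are harder to meet than the table in Step 3 shows.

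**Step 5: false triggers if the major class is widened.** With equal rates in both arms and p < 0.1, the chance is 0.8% at a 1% rate, 6.5% at 3% and 10.5% at 5%.

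**The case against.** **Plexus injury.** A reader might infer that every persistent plexus injury is treated as minor. The text does not support that. The plexus injury in the Discussion is iatrogenic; when caused at operation it is nerve damage, and the definition makes it major if it persists. The document nowhere names a delayed, persistent plexus lesion as an ESIN risk. Only the literal gap for lesions first recorded after surgery remains.

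**Final report.** A reader might also infer that the trial would publish these events as minor. Statistical Methods compares complication frequency without a major/minor split, and Table 4 lists complications by time point. The split is used only for interim monitoring.

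**Rarity.** Thoracic perforation appears once, as a precaution, and surgeons must have done over 20 procedures with each technique. Nothing in the document supports a rate of 5% or 10%. This stands: for a rare event, reclassification alone would seldom trigger a stop.

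**Design choice and oversight.** The split is explicit and exhaustive, the DSMB includes two surgeons and also sees minor complications, and serious-event procedures may sit in the full protocol. That limits the practical damage. But the definition and the criteria that depend on it are stated text, and the only discretion written into them is for mortality.

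**Overreach in a remedy.** Extending the severity test to every post-operative complication could move malunion, non-union or scarring into the major class and raise false triggers. This stands, and it limits the fix.

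**Conclusion.** The point holds in a limited form. The major class is restricted by type of damage and by timing, not by severity. A thoracic perforation with prolonged admission but no qualifying re-operation or death is therefore minor, as is, read literally, a persistent plexus lesion first recorded after surgery.

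The minor criterion barely responds to such events: its trigger chance rises from 0.8% with no excess to 1.6% and 4.3% at excesses of 5% and 10%, against 26.9% and 62.9% under the major criterion. These figures assume 36 per arm, an uncorrected chi-square, independence, the protocol's lower rates as background and a trigger on the p-value alone. Under Fisher's test the contrast is smaller (0.8% v 4.3% and 2.4% v 27.2%) but runs the same way.

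It would be too strong to say that correcting the class ensures a stop for rare serious harm: at an excess of 2% or less the major threshold is reached in under 7% of trials.

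**What to change.** Reconcile the DSMB definition with Table 3, the ESIN procedure and the Discussion:

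- Apply the existing severity test (prolonged admission, persistent injury or death) to any intra-operative complication, including those in the catch-all item.
- Apply it also to nerve lesions first recorded after surgery that persist, and give these a place in Table 3 separate from the transient item.
- Leave wound, implant and union items classified as now, major only if re-operated.
- Leave the differences and p-thresholds unchanged.

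The cost is a change of wording plus a record of whether each event prolonged admission or persisted. Complications are already registered at every visit, and 25 of 120 patients had been included when the article was written, so at that point the planned 72-patient interim look was still ahead. The downside is that the major rate may rise above the planned 1%, and with it the chance of a false trigger (0.8% at a 1% rate in both arms, 6.5% at 3%). The DSMB should know this when it adopts the wording.

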### End Points

The primary endpoint is the DASH score 6 months after surgery. Secondary endpoints are listed in table 4.

**Table 4 T4:** Primary and secondary endpoints

Primary Endpoint	Secondary Endpoints
- DASH score after 6 months	- Constant Score after 6 months
	- DASH and Constant Score after 6 weeks, 3 months and 1 year
	- Complications: intra-operative, post-operative period (2 weeks) and after 6 weeks, 3 and 6 months and 1 year
	- Reoperation after unsatisfying result in a time horizon of 1 year (including implant removal)
	- Time to radiological consolidation, with a maximum time horizon of 6 months
	- Pain score, until 2 weeks postoperative
	- Cosmetic satisfaction after 6 months and 1 year

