### Current status

This study has been approved by the Medical Ethics Committee of the Diakonessenhuis Utrecht. Approval of the local Ethical Boards of the other two participating hospitals is currently requested. This study is performed in accordance with the ethical standards of the Declaration of Helsinki. Recruitment of patients started in January 2011 in the Diakonessenhuis, Utrecht and will start in April 2011 in the Medisch Centrum Haaglanden, The Hague and St. Elisabeth Hospital, Tilburg. To date 25 patients have been included in the study. After a start-up phase the speed of the inclusion is expected to increase steadily and, depending on the number of patients needed to be included in the trial (see sample size considerations), recruitment of the 120^th ^patient is currently expected in July 2012. Analysis and reporting is subsequently expected one year later to be complete (July 2013). The POP study is registered in the Dutch Trial Register (NTR 2438).

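### The interim DASH criterion (p = 0.003, 16.5% power) belongs to a look at 50% information, but the look is set at one year with 72 patients included, which gives a different fraction

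*Protocol article*

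**What the plan says.** All references are to the protocol article. Under End Points: "The primary endpoint is the DASH score 6 months after surgery". Sample Size and Power starts from an SD of 11, a two-sided alpha of 0.05 and 80% power, and concludes: "53 patients in each group are needed (total 106) to show a difference of at least 6 points in DASH score after 6 months". The same section allows for the interim: "it is assumed that 2 sequential tests are made using the O'Brien-Fleming spending function to determine the test boundaries". It then adds an allowance for 10% loss, which brings the number to be included to 120.

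The section on the data and safety monitoring board sets the interim analysis at one year and expects: "After one year, 72 patients (36 patients in each arm) will be included if inclusion is moving on as expected". Its DASH stopping criterion is "an established difference in DASH-score with an effect size of 0.55 with a two-sided p-value of 0.003 and 16.5% power", tied in the same bullet to the first of the two sequential tests of the primary outcome. Nowhere is the look tied to a number of patients with a 6-month DASH or to an information fraction.

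On accrual, Current status reports 25 patients already included, recruitment from January 2011 in one hospital, the other two hospitals due to start in April 2011, the 120th patient expected in July 2012, and: "After a start-up phase the speed of the inclusion is expected to increase steadily".

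**The concern.** Under a spending function, the significance level at a look depends on how much of the final information is available then. A printed level of 0.003 and a printed power of 16.5% therefore imply a particular number of patients with the primary outcome. If the scheduled look has a different number, the monitoring board holds a threshold that the named function would not give, and a power that does not describe its look.

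A 6-month outcome makes this acute, because at a one-year look the patients counted as included are not the patients with the outcome. The criterion also gives no time point for the DASH, although Follow-up collects it at 6 weeks, 3 months, 6 months and 1 year. A board short of 6-month scores might turn to earlier visits, which are secondary endpoints.

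**Working it through.** **Inputs.** From Sample Size and Power: difference 6, SD 11, two-sided alpha 0.05, power 0.80, 106 evaluable patients, two looks, O'Brien-Fleming spending, 10% loss. From the monitoring section: one year, 72 included, effect size 0.55, p = 0.003, power 16.5%. From Current status: the accrual facts above.

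**Sample size.** n per arm = 2 × [(1.960 + 0.842) × 11/6]² = 52.8, so 53 per arm and 106 in total, as stated. 106/0.9 = 117.8, so 118, taken up to 120.

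**Boundary.** For the O'Brien-Fleming-type (Lan-DeMets) spending function, the two-sided level at a first look with information fraction t is p(t) = 4 × [1 − Φ(2.2414/√t)], where 2.2414 is the normal quantile at 1 − 0.05/4. At t = 0.50, p = 0.00305 (z = 2.963), which rounds to the stated 0.003. The classical two-look O'Brien-Fleming boundary (z = 2.797) gives 0.0052 and does not match.

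**Power.** Power = 1 − Φ(2.968 − d√(n/2)), with 2.968 the critical value for 0.003. With n = 26.5 per arm it is 16.3% for d = 6/11 and 16.7% for d = 0.55, against 16.5% stated.

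**Solving backwards.** p(t) rounds to 0.003 only for t from 0.482 to 0.513, and power of 16.5% needs t of about 0.50. The stated pair therefore implies about 53 of 106 patients.

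**The scheduled look.** The year is taken to run from the start of recruitment. The split of the 72 over the year is not stated, so each row is an assumption. Power is for d = 0.55 (normal approximation).

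| Assumption | With 6-month DASH | Fraction | Spending p | Power at 0.003 | Power at spending p |
|---|---|---|---|---|---|
| All 72 counted | 72 | 72/106 = 0.68 | 0.0131 | 26% | 44% |
| All 72, less 10% loss | 64.8 | 0.61 | 0.0083 | 23% | 33% |
| Fraction taken as 72/120 | (63.6 of 106) | 0.60 | 0.0076 | 22% | 32% |
| **Reproduces the plan** | **53** | **0.50** | **0.00305** | **17%** | **17%** |
| Early rate continues: 25 per 3 months | 50 | 0.47 | 0.0022 | 15% | 13% |
| 25 by month 3, then constant to 120 at month 18: 25 + 95 × 3/15 | 44 | 0.42 | 0.0010 | 13% | 7% |
| 25 by month 3, then constant to 72 at month 12: 25 + 47 × 3/9 | 40.7 | 0.38 | 0.0006 | 11% | 5% |
| Uniform: 72 × 6/12 | 36 | 0.34 | 0.00024 | 9% | 2% |
| Uniform, less 10% loss | 32.4 | 0.31 | 0.00010 | 8% | 1% |

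Placing the 25 patients by month 3 is itself an assumption, drawn from the text speaking of April 2011 as still to come. The 47% row implies 100 patients at one year, more than the expected 72. Reaching 53 would need 53 of the 72 included in the first half-year, which does not fit inclusion that speeds up. The 6 months also run from surgery, which may follow the injury by up to 4 weeks (Interventions).

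**On the DASH scale.** The observed difference that crosses a boundary is z × 11 × √(4/N). With N = 36 it is 10.9 points at 0.003 and 13.5 at the spending boundary. With N = 72 it is 7.7 and 6.4 points.

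**Overall type I error.** With p = 0.003 at the look and a final critical value of 1.969 (the value that goes with t = 0.50), the two-sided error is 0.0507 at t = 0.31, 0.0506 at 0.34, 0.0500 at 0.50 and 0.0494 at 0.68.

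**The case against.** The strongest reply is that the 72 was never meant as the DASH sample. It is conditional on recruitment going as expected, and it suits the minor-complication criterion, which needs 37 per arm and has 79% power at 36. The DASH line would then carry the planning boundary for two equally spaced looks. A spending function exists so that the boundary can be recomputed, and that step often sits in a monitoring charter or analysis plan not shown here. This is a plausible account of how the figures arose. It does not remove the mismatch: the text prints 0.003 as the stopping level for the one-year look and does not mark it as a planning value.

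Three stronger readings are tempting, and the protocol does not support them.

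- **No reading gives 50%.** The criterion names no DASH time point. With the 3-month score and uniform accrual, 54/106 = 0.51, with spending p = 0.0034 and 17% power at 0.003. This is not the better reading, because the criterion refers to the primary outcome, which is at 6 months, but the text leaves it open.
- **The fraction cannot exceed 0.34, so 0.003 is more than ten times too lenient.** The ratio 0.003/0.00024 = 12.5 belongs to uniform accrual alone. Counting the 25 early patients gives ratios of about 5 (at 0.38) and 3 (at 0.42), and 1.4 at 0.47.
- **The trial's type I error is inflated.** It is not, to any material degree, as the last step of the working shows.

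**Conclusion.** The criterion is wrong as written: its threshold and its power describe a look at about 53 of 106 patients, and the look scheduled is a different one. If all 72 counted, 0.003 would be too strict (the spending function allows 0.0076 to 0.013) and power at 0.003 would be about 22 to 26%. On the 6-month DASH the fraction is about 0.31 to 0.47, so 0.003 is too lenient, by an amount that depends on accrual, and power at 0.003 is about 8 to 15%.

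The reproduction at 50% information rests only on the protocol's own figures. The size of the departure rests on assumed accrual profiles and on the year running from the start of recruitment.

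The harm is a wrong early-stopping boundary and a wrong stated interim power given to the monitoring board. Overall two-sided type I error stays at about 0.049 to 0.051 with the matching final critical value. If the final test used 0.05, as Statistical Methods states for all analyses, it would be about 0.050 to 0.052, but most of that excess comes from the final level and is present at t = 0.50 too (0.0510). This should be fixed, but it does not threaten the validity of the trial.

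**What to change.** Keep the one-year safety review as it is. For the DASH, choose one of two wordings.

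1. Hold the DASH look when about 53 patients have a 6-month score, and keep 0.003 and 16.5%.
2. Keep the one-year date, compute the boundary from the named spending function at the observed fraction (patients with a 6-month DASH divided by 106), restate the power for that number, and mark 0.003 as the planning value at 50% information.

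Under either, say that the score tested is the 6-month DASH, and take the final critical value from the same calculation.

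The first option costs a somewhat later DASH look. The second costs a less favourable stated interim power, for example about 2% at 36 evaluable patients. Neither needs more patients; the change is to the protocol text and the monitoring board's instructions.
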